## Abstract

**Background:**

Chronic pain (CP) has serious medical and social consequences and leads to economic burden that threatens the sustainability of healthcare services. Thus, optimized management of pain tools to support CP patients in adjusting to their condition and improving their quality of life is timely. Although acceptance and commitment therapy (ACT) is considered an evidence-based psychological approach for CP, evidence for the efficacy of online-delivered ACT for CP is still scarce. At the same time, studies suggest that self-compassion mediates the change in disability and psychopathological symptoms in ACT interventions for CP, although self-compassion is not a specific target in ACT. Thus, an explicit focus on self-compassion might increase the efficacy of ACT interventions for CP, although this hypothesis has not been tested. This study aims to develop an eHealth ACT and compassion-based self-management intervention for CP, the iACTwithPain, and to compare its efficacy in improving health outcomes to a similar ACT-only intervention and a medical TAU group.

**Methods:**

The eHealth platform that will host the interventions will be developed using a flat design identity and will be interactive. The iACTwithPain intervention will comprise eight weekly self-management sessions and will be developed taking into consideration the psychological flexibility model applied to CP, with the addition of explicit compassion-based components. To analyze whether the iACTwithPain intervention will present superiority in improving CP’s impact and related health markers over the two other conditions, this study will follow an RCT design with three arms. CP patients will be recruited through direct contact with patient associations and healthcare services and a national press release in Portugal. Outcome measurement will be conducted at baseline, post-intervention and at 3- and 6-month follow-ups. The interventions’ acceptability will also be assessed.

**Discussion:**

The iACTwithPain intervention is expected to improve CP patients’ psychosocial functioning, quality of life, and empowerment, by promoting adaptive disease management and regulation of pain-related internal experiences. Results will contribute to a better understanding on the pertinence of adding compassion elements to ACT for CP and to reach an optimized intervention for CP.

**Clinical Trial Registration:**

This trial has been registered at ClinicalTrials.Gov (NCT04200183; 16 December 2019; https://clinicaltrials.gov/ct2/show/NCT04200183). The current manuscript comprises the first version of this clinical trial’s protocol.

## Background

Chronic pain (CP), defined as sporadic or constant pain or discomfort lasting for more than 3 months (Elliott et al., 1999), is a major public health issue that affects 19% of adult Europeans and impairs the quality of their social and working lives (Breivik et al., 2006). In Portugal, a recent study estimated that CP has a median duration of 10 years, with 85% of CP patients with recurrent or continuous pain and 68% of CP patients with moderate to severe pain intensity (Azevedo et al., 2012). In addition, CP yields a great economic burden to the healthcare system and society at large. It is estimated that CP presents serious costs to economics and health services (Phillips, 2009). Moreover, evidence suggests that up to 50% of non-malignant pain patients are addicted to pain medication (Højsted and Sjøgren, 2007), which leads to further health problems (Højsted and Sjøgren, 2007) and imposes a cost burden on health systems (Shei et al., 2015).

Chronic pain is a multifaceted experience that results from an interplay of physiological states and psychological processes (i.e., thoughts, emotions), and current approaches to CP recognize the value of addressing the cognitive and affective aspects of pain (Eccleston et al., 2013). Studies show that CP is associated with psychiatric disorders (Dominick et al., 2012), with a significant impact on the quality of life and functioning of CP patients (Breivik et al., 2006). However, the current provision of care to CP sufferers vastly disregards psychological interventions. Also, traditional psychological interventions for CP focus primarily on controlling pain and overall symptoms’ reduction. Nonetheless, research has shown that an exclusive and overly focus on pain control might be frustrating and damaging and actually result in more disability (McCracken, 1998), higher pain intensity, pain-related anxiety, and depression (McCracken and Vowles, 2006).

In contrast, for the last two decades the evidence has suggested that acceptance of pain is a major key process in successfully adapting to CP (Vowles et al., 2007; Vowles and McCracken, 2008) and is associated with less pain, disability, depression, and pain-related anxiety (McCracken and Eccleston, 2003). This led to a growing interest in acceptance-based approaches, focusing not so much in reducing and controlling pain, but rather in increasing the acceptance of pain (Costa and Gouveia, 2013; Pinto-Gouveia et al., 2015).

Acceptance and commitment therapy (ACT), which focuses on function improvement rather than symptom reduction, is an empirically supported intervention for CP (APA Presidential Task Force on Evidence-Based Practice, 2006). An ACT intervention for CP aims to promote emotional acceptance and engagement with values-consistent actions, despite CP symptoms (Hayes et al., 1999; Vowles et al., 2007; Vowles and McCracken, 2008). Recently, some studies suggested that ACT interventions also promote self-compassion (Yadavaia et al., 2014; Luoma and Platt, 2015), a non-judgmental and mindful approach to one’s pain and suffering (Neff, 2003), which presents known links with pain regulation systems, such as heart-rate variability (Rockliff et al., 2008), and oxytocin-endorphin systems (Rockliff et al., 2011). Self-compassion has been the focus of growing attention in CP due to its protective role against depressive symptomatology in this condition (Carvalho et al., 2019), its negative association with pain disability (Wren et al., 2016), and the promising results showing the positive effects of compassion-based interventions in CP (Chapin et al., 2014; Ziemer et al., 2015; Parry and Malpus, 2017; Gooding et al., 2020).

Interestingly, self-compassion appears be associated with important ACT processes (Costa and Pinto-Gouveia, 2013; Carvalho et al., 2018a; Edwards et al., 2019), and although ACT interventions do not specifically incorporate explicit self-compassionate exercises, self-compassion was found to mediate the change in disability and psychopathological symptoms in an ACT intervention for CP (Vowles et al., 2014). This raises the possibility that self-compassion may be an under-recognized mechanism of change in ACT and that an explicit focus on self-compassion in ACT might increase the efficacy of ACT interventions. Further, although ACT interventions with elements from compassion-based approaches seem to significantly improve mental health in a number of clinical populations (Skinta et al., 2015; Palmeira et al., 2017; Pinto-Gouveia et al., 2017; Trindade et al., 2020), the individual role of self-compassion in ACT for CP and the benefit of adding explicit compassionate exercises to such interventions are still unclear.

There is a growing interest in using online interventions to improve health (i.e., eHealth). In fact, eHealth is expected to contribute to the sustainability of healthcare systems, with advantages such as reducing therapist time and waiting lists, increased cost-effectiveness, ability of patients to work at their own pace, accessibility to large clinical samples, and accessibility to rural and remote clinical cohorts (Bergmo, 2015). Also, it seems to provide an effective way of dealing with the inadequate training of health professionals in the psychological aspects of CP and of bypassing the shortage of psychological therapists in the national healthcare system. Some studies tested the efficacy of online ACT interventions for CP (Buhrman et al., 2013; Trompetter et al., 2014; Fledderus et al., 2015; Vilardaga et al., 2020), which resulted in reduction of pain intensity, pain-related distress, anxiety and depressive symptoms, and an increase of activity engagement and pain-willingness (Buhrman et al., 2013). However, there were several methodological limitations to these studies (small sample size and non-randomization). Further research is thus needed to better comprehend the efficacy of eHealth ACT interventions for CP and, in addition, the contribution of self-compassion to this approach.

### Aims of This RCT

This study has three main aims: (1) to develop an ACT and compassion-based eHealth tool for CP management (iACTwithPain); (2) to analyze whether the iACTwithPain intervention will present superiority in improving CP’s impact and related health and quality-of-life markers over an ACT-only intervention and a wait-list condition; and (3) to examine whether the interventions’ efficacy will be explained by changes in therapeutic processes (e.g., self-compassion and psychological flexibility).

We hypothesize that the platform will present high acceptability and that both the ACT-only and iACTwithPain interventions will have efficacy in improving CP’s impact, mental health, and quality of life. Further, we also hypothesize that the intervention with explicit self-compassion components, the iACTwithPain, will present superiority in decreasing self-criticism and increasing self-compassion, quality of social relationships, and social safeness through the activation of the affiliative system and subsequent stimulation of oxytocin activity. The efficacy of the ACT-only intervention is expected to be explained by increases in psychological flexibility and mindfulness abilities, and decreases in cognitive fusion and rumination. The iACTwithPain intervention’s efficacy is expected to be explained by changes in the same processes and, in addition, by changes in self-compassion and self-criticism (Figure 1).

**FIGURE 1 F1:**
[figure not shown]
Examples of session screens. This study’s team holds the copyright of this image.

## Methods/Design

This study is funded by the Portuguese Foundation for Science and Technology and is registered at ClinicalTrials.gov (Identifier: NCT04200183, date assigned 16/12/2019). Ethical approval has been obtained from the Ethics Committee of the Faculty of Psychology and Education Sciences of the University of Coimbra. Eventual protocol amendments will be communicated to this Committee.

### Participant Recruitment

Recruitment will be facilitated by advertisement in Portuguese press and social media. Individuals interested in the study will sign up in the platform and then be asked to sign an informed consent fill out questionnaires designed to assess inclusion and exclusion criteria.

### Participant Selection

Patients are eligible to participate if they:

•are aged between 18 and 50 years;•have had a CP diagnosis for the last 3 months;•have access to internet and willingness to do it regularly (at least once a week);•are willing to be randomized;•can read and write Portuguese; and•can give informed consent.

Patients are ineligible to participate if they:

•are undergoing any other form of psychological intervention for CP;•present a severe psychiatric problem (e.g., severe depression, psychotic illness, bipolar disorder, and borderline personality disorder)—assessed using several questions (self-reported) based on the diagnostic criteria according to DSM-V; and•present pain due to malignancy, trauma, or surgery.

Participants who do not meet the eligibility criteria will be given feedback and advised to seek medical/psychological/group support.

### Sample Size

Results from G^∗^Power calculations for repeated measures analysis, assuming a *p*-value = 0.05, an effect size of *f* = 0.25 (Scott et al., 2018), with a statistical power of 0.95, three groups, and four measurements, recommend a sample size of 171. Giving the 30% drop-out rate in previous ACT-based intervention studies (Melville et al., 2010), the total sample size to be collected will be 246 (each group will be composed of 82 participants).

### Randomization of Participants

Participants will be randomized (computer-generated random allocation) to one of three conditions: experimental condition 1 (ACT-only intervention); experimental condition 2 (iACTwithPain + self-compassion); and control condition (medical TAU). All participants will continue their treatment as usual for CP. Each participant will be randomly assigned with a number between 1 and 246; after number assignment, participants with numbers 1–82 will be allocated to experimental condition 1, 83–164 to experimental condition 2, and 84–246 to the control condition. Only participants from the experimental conditions will be blind to their allocation; we do not expect any need for unblinding participants in these conditions.

Participants in the two experimental conditions will then access to the respective version of the platform, where they will be asked to complete pre-intervention questionnaires (T0). The control group will only be provided access to the questionnaires.

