### The ACT-Only Intervention

The ACT-only intervention will follow the same structure and contents as iACTwithPain’s, with the exception of sessions 5 and 6, which, instead of presenting compassion elements, will reinforce and further address willingness, acceptance, defusion, and observing self topics, without adding new information or practices. This intervention will be delivered via the same platform as the iACTwithPain intervention.

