### Primary and Secondary Outcomes in the RCT

Before (T0) and after (T1) the interventions, and in the 3-month (T2) and 6-month (T3) follow-ups, participants in the experimental conditions and in the waiting-list control condition will be assessed through several self-report questionnaires. Participants will receive notifications via email to complete the self-report measures. These data will be collected in the iACTwithPain platform using high standard security mechanisms which will ensure confidentiality. Only the research team will have access to the collected data, including the final dataset, which will be managed by the study’s PI (PC) and kept for 5 years after the study ends. Participants will only be identified by a generated code.

Participants will provide sociodemographic and clinical information and complete self-report measures (in their validated Portuguese versions) to assess primary and secondary outcomes see Table 2.

**TABLE 2 T2:** Schedule of enrollment, interventions, and assessments.

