	**Study period**					
	**Enrollment**	**Allocation**	**Post-allocation**			
**Timepoint**	** *-t_2_* **	** *-t_1_* **	** *t* _0_ **	** *t* _1_ **	** *t* _2_ **	** *t* _3_ **

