## Discussion

To our current knowledge, iACTwithPain will be the first eHealth intervention that incorporates ACT and explicit self-compassion elements. This intervention is expected to improve CP patients’ psychosocial functioning and quality of life, by promoting adaptive disease management and regulation of pain-related internal experiences. By providing access to specialized treatment with an online delivery format and self-management nature, the intervention is also expected to promote patients’ empowerment and accessibility to treatment. Results will contribute to better understand self-compassion’s individual role in ACT for CP, the pertinence of adding compassion-promoting exercises to those interventions, and to reach an optimized intervention for this population.

One of this study’s strengths is the analysis of the potential mechanisms of change of the tested interventions, which will shed light on which therapeutic processes are responsible for improvements in CP, in both the iACTwithPain intervention and the ACT-only intervention. Another strength is the platform itself, which will be developed aiming at being intuitive and graphically attractive and which will track participants’ interaction, providing objective data on participants’ between-session practice and engagement with the interventions, which will be examined and accounted for in the efficacy test.

One of the most significant challenges will be the prevention of drop-outs. A strategic way of decreasing this risk will be to email participants with supportive and motivating messages every time the platform registers inactivity for more than 3 days. Another limitation will be that participants allocated to the control group (medical TAU) will not be blind to their allocation due to the nature of this condition, which might influence self-reported outcomes.

In conclusion, this study will contribute with a new eHealth self-management intervention for CP, which, if proven effective, will significantly help CP patients manage their pain and improve their mental health and quality of life and improve accessibility to treatment of remote clinical cohorts or with limited mobility. With this RCT, specific knowledge will be obtained about the role of self-compassion in ACT for CP and the potential benefits of adding explicit self-compassion elements to ACT.

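### Baseline (T0) is collected after allocation, with controls unblinded, which leaves the three-arm test and the active-versus-control contrasts open to an allocation-induced shift in T0 and to differential T0 non-completion

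*Protocol article*

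**What the plan says.** All of this is in the Protocol article.

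- **Order of events, Randomization of Participants.** Participants are randomised to three conditions, and T0 comes only after that. Those in the active arms fill it in once admitted to their own arm's site: "where they will be asked to complete pre-intervention questionnaires (T0). The control group will only be provided access to the questionnaires".
- **Schedule, Table 2.** Consent, eligibility screening and randomisation are marked in the enrolment column and allocation in the next. The columns t0 to t3 all stand under "Post-allocation". Text and table agree, so this is the stated design.
- **Blinding, Randomization of Participants.** "Only participants from the experimental conditions will be blind to their allocation". The Discussion concedes that controls "will not be blind to their allocation due to the nature of this condition, which might influence self-reported outcomes", but does not apply this to T0.
- **Before allocation, Participant Recruitment.** People sign up on the platform, consent and "fill out questionnaires designed to assess inclusion and exclusion criteria". No outcome scale is listed at this step.
- **Timing relative to treatment, Primary and Secondary Outcomes in the RCT.** Assessments fall "Before (T0) and after (T1) the interventions" and at 3 and 6 months, by self-report questionnaire.
- **Analysis, Statistical Analysis.** A repeated-measures MANOVA tests the within-between interaction over the four occasions, T0 included. Missing data are to be imputed.

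**The concern.** A baseline is comparable between arms because it is fixed before anyone can know the allocation. Here T0 lacks that protection. A person who has just been given questionnaires only may describe pain impact, mood or quality of life differently from a person who has just been admitted to an intervention platform. Because T0 is one of the occasions in the interaction test, such a difference enters the estimated change even if the treatments do nothing.

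There is a second route. A participant may leave between allocation and T0, and the two situations differ enough that the loss could differ by arm. That person is randomised but has no outcome measurement.

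At stake are the superiority of iACTwithPain over the wait-list and the hypothesis that both interventions are efficacious, since both rest on comparisons with the control arm. A later analysis plan cannot recover a pre-randomisation baseline that was never collected.

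**Working it through.** **1. The plan's own figure.** Inputs from Sample Size: alpha 0.05, f = 0.25, power 0.95, k = 3 groups, m = 4 occasions. For a MANOVA within-between interaction (Pillai trace):

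- s = min(k−1, m−1) = 2
- df1 = (k−1)(m−1) = 6
- df2 = s(N − k − (m−1) + s) = 2 × (171 − 3 − 3 + 2) = 334
- lambda = s × f² × N = 2 × 0.0625 × 171 = 21.4

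Power at N = 171 is 0.951, and 171 is the smallest N that reaches 0.95. For dropout, 171/0.70 = 244.3, so 245, and 246 as a multiple of three. The plan's 171 and 246 reproduce. The order of T0 and allocation does not enter this calculation.

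**2. Bias from a T0 shift.** Assume no true effect, equal variances, and correlation rho between occasions. Control T0 alone shifts by d SD, and a fraction p of the shift is still present at follow-up. The documents give no value for d, p or rho. Active minus control is then:

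- change score: (0 − 0) − (pd − d) = d(1 − p)
- T0 as covariate: −pd + rho × d = d(rho − p)
- follow-up score alone: −pd

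If the shift is gone by T1 (p = 0), these are d, rho × d and 0. With d = 0.2 and rho = 0.5, they are 0.2, 0.1 and 0 SD. If the shift persists fully (p = 1), the change-score bias is 0. None of the three is unbiased for every p.

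**3. Effect on the planned test.** The group-by-time MANOVA was simulated for one outcome with no true effect, p = 0, alpha 0.05 and 3,000 replicates per cell. The 57 per arm is 246 × 0.70/3 = 57.4, rounded down. Entries are rejection rates.

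| n per arm | rho | d = 0 | 0.1 | 0.2 | 0.3 | 0.5 |
|---|---|---|---|---|---|---|
| 82 | 0.5 | 0.05 | 0.09 | 0.21 | 0.48 | 0.94 |
| 82 | 0.7 | 0.05 | 0.11 | 0.34 | 0.74 | 1.00 |
| 57 | 0.5 | 0.05 | 0.08 | 0.17 | 0.33 | 0.82 |
| 57 | 0.7 | 0.05 | 0.09 | 0.25 | 0.55 | 0.97 |

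The test has no direction, so the sign of d does not alter these rates. The sign does decide whether a benefit over control is overstated or understated. At a given d, the larger sample rejects more often, because the error is systematic.

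**4. The two active arms.** Both are blind to which intervention they receive and complete T0 under like conditions on the same platform. The ACT-only content follows iACTwithPain's "with the exception of sessions 5 and 6". In the model neither arm is shifted, so their contrast has zero bias.

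**5. Loss before T0.** The only questionnaires described before T0 are for eligibility. A participant who leaves between allocation and T0 therefore has no outcome data described from which to impute. One who misses T0 but answers later could be imputed. The documents give no rate for either.

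**The case against.** The strongest reply is that T0 is described as preceding the interventions, so nobody has been treated when it is completed, and that being on the platform is not exposure to its content. This stands as far as treatment exposure goes, although the article does not say whether T0 comes before introductory session 0. It does not answer the point about allocation: knowing one's assignment may be enough to change a self-report. The article does not state when controls learn their assignment. That they know it by T0 is an inference, but a natural one, since they are assigned first and then receive questionnaires only.

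A reader might infer more than the documents support:

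- **That every change-from-T0 comparison is affected.** The contrast between the two active arms, which carries the question about added compassion, is not shown to be.
- **That T0 is in fact contaminated or selectively missing.** Both are risks. No figure or rule in the article shows either occurring, and imputation is planned.
- **That the shift always passes in full into the change score.** That holds only if it has gone by follow-up. Controls stay unblinded throughout, so some of it may persist and cancel.
- **That the bias is a known share of the planned effect.** The article gives f = 0.25 for three groups and four occasions. It gives no pairwise difference to divide by.

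It is also fair to say that the Discussion already discloses the unblinded control arm as a limitation. It does so for self-reported outcomes in general and leaves the order of T0 and allocation unaddressed.

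**Conclusion.** The point holds for the three-arm interaction test and for each active arm against control. T0 follows allocation, controls are not blind, the scales are self-reported, and the test uses T0. The size and direction of any bias are unknown. Under the assumptions that only control T0 shifts, by d SD, and that the shift fades by T1, the change-score bias is d and about rho × d remains after covariate adjustment. For assumed shifts of 0.1 to 0.3 SD with 82 per arm, the false rejection rate runs from 0.09 to 0.48 at rho 0.5 and from 0.11 to 0.74 at rho 0.7. With a persisting shift the change-score bias is smaller, down to none. Differential loss before T0 is possible but not documented. The weakness is in the order of data collection, so it has to be corrected before participants are enrolled.

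**What to change.** Have every consenting, eligible participant complete the full T0 battery in the existing sign-up and eligibility step (Participant Recruitment). Trigger the computer allocation only when T0 has been submitted. Rewrite the order in Randomization of Participants, and correct Table 2 so that t0 stands before allocation.

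The cost is a change in platform workflow and a longer sign-up step. Some people may stop there, but they will not have been randomised, so the comparison of arms is untouched. No assessment is added, and the sample size stays at 171 before and 246 after dropout. The change does not address unblinded self-report by controls at T1 to T3, which remains the limitation stated in the Discussion.
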